#### Primary analysis set

This data set defines the cohort of patients based on which the primary confirmatory efficacy analysis is performed. The primary analysis set consists of all recruited patients excluding those with a pathologically defined uninformative VAB sample tissue (“Category C”: unclear representative or not representative VAB).

#### Secondary analysis set

The Secondary Analysis set consists of all recruited patients including those with an unclear representative or not representative VAB sample tissue in the histopathological assessment. This data set defines the cohort of patients and subsamples based on which the secondary descriptive analyses are performed (see below “Secondary Analysis”).

### Analysis strategy

#### Primary efficacy analysis

The null hypothesis to be assessed within the confirmatory analysis states that the rate of patients with non-detected residual tumor p is larger or equal to 0.1. Whereas the alternative hypothesis, for which this trial is powered, states that p is at most 0.05. The test hypotheses are thus given by.

H0: *p* ≥ 0.1 versus H1: *p* < 0.05,

which are tested with the one-sample Binomial-test at a one-sided significance level of α = 0.025.

The rate of patients with non-detected residual tumor p is estimated by the number of cases with diagnosed bpCR in VAB divided by the number of all patients for which surgery or VAB revealed a residual tumor.

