**Table Taba:** 

Category A	Residual tumor cells in VAB specimen (= non-bpCR)
Category B	No residual tumor cells in the VAB specimen and VAB representative of former tumor region (= bpCR in VAB)
Category C	No residual tumor cells in the VAB specimen but VAB unclear representative or not representative of former tumor region (= possible sampling error)

Category C VABs are categorized as uninformative for the primary endpoint of the clinical trial.

The investigators assume that there is no difficulty to diagnose a “Category A” VAB result. The challenging topic is defining a VAB specimen to be pathologically representative of the former tumor region (tumor bed) or not, i. e. to differentiate between “Category B” and “Category C”. Only representative VAB samples are informative.

To evaluate intra- and interrater reliability of pathological evaluation of VAB specimen all local pathologists will be asked to send pre-NACT biopsy specimen and post-NACT VAB specimen (H&E sections or virtual microscopy files) of all non-tumorous VABs to the Department of Pathology Heidelberg (“pathological sub-study”). Slides will be digitized, pseudonymized, and returned to different local pathologists. Intra- and interrater reliability evaluation will be performed by at least five pathologists participating in the trial.

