### Outcomes and measurements

The primary outcome is the false negative VAB result, i.e. the non-detected residual tumor by VAB compared to breast surgery. We will report this outcome as the false negative rate (FNR = rate of patients with non-detected residual tumor by VAB compared to breast surgery) which is a commonly used and validated measure in diagnostic studies. The FNR will serve as outcome measure in the cohort of the confirmatory primary outcome analysis. It will be calculated as the quotient of the number of cases with bpCR in VAB (“Category B”) and residual tumor in surgical specimen (false negative VAB results), divided by the total number of cases with residual tumor in either specimen (VAB and / or surgical specimen). Residual tumor is defined as a positive result, in surgical specimen as well as in VAB.

As our secondary outcomes we will use true negative and true positive results compared to breast surgery. The standard definitions are applied.

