### Analysis variables

#### Derivation of the primary endpoint

The false negative rate (FNR) will be calculated as the quotient of the number of cases with “pCR in VAB” and residual tumor in surgical specimen (false negative VAB results), divided by the total number of cases with residual tumor in surgical specimen and / or VAB in the cohort of the confirmatory primary outcome analysis (= primary analysis set).

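### The estimator sentence for the confirmatory test omits the surgical-residual condition that the protocol's own definition of the false negative rate requires

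*Protocol article*

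**What the plan says.** The protocol article gives the numerator of the primary rate in three places.

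- **Outcomes and measurements:** the false negative rate is defined by "bpCR in VAB (“Category B”) and residual tumor in surgical specimen (false negative VAB results), divided by the total number of cases with residual tumor". Tumour in the biopsy or at surgery qualifies a patient for the denominator.
- **Derivation of the primary endpoint:** the same numerator, "pCR in VAB” and residual tumor in surgical specimen (false negative VAB results", applied to the primary analysis set.
- **Primary efficacy analysis:** the estimator of p reads "estimated by the number of cases with diagnosed bpCR in VAB divided by the number of all patients for which surgery or VAB", where the denominator again means patients with tumour found in either specimen. There is no condition on the surgical specimen in the numerator.

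The category table under Intervention assignment and blinding defines Category B as "No residual tumor cells in the VAB specimen and VAB representative of former tumor region (= bpCR in VAB". That label depends on the biopsy alone.

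The null hypothesis is that "the rate of patients with non-detected residual tumor p is larger or equal to 0.1". The alternative "states that p is at most 0.05". The test is a one-sample binomial test at one-sided α = 0.025.

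**The concern.** The Primary efficacy analysis section tells the analyst what to compute for the only confirmatory hypothesis. Its numerator differs from the one that defines the endpoint. A Category B biopsy followed by tumour-free surgery is a true negative. The written numerator counts that patient, and the denominator does not.

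The numerator is then not a subset of the denominator, so a binomial test of the count against the denominator has no valid basis. In some settings the count would exceed the number of trials. The Discussion makes rejection of this null hypothesis the ground for rating the biopsy as accurate, so its estimator should not have to be inferred.

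**Working it through.** **1. Reproduce the plan's own figure.** Inputs: p0 = 0.10, p1 = 0.05 and one-sided α = 0.025 (Primary efficacy analysis); power 0.8 (Sample size calculation). Under the normal approximation with separate null and alternative variances:

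n = [(z₀.₉₇₅·√(p0(1−p0)) + z₀.₈₀·√(p1(1−p1))) / (p0 − p1)]²

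= [(1.960 × 0.3000 + 0.8416 × 0.2179) / 0.05]² ≈ 238.03

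This matches the stated 238 cases, and 238 / 0.5 = 476 patients. An exact binomial check at n = 238 rejects with 14 or fewer false negatives (attained α 0.0170, power 0.786). The design was therefore sized on false negatives among patients with residual tumour.

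**2. Write the two estimators in the same terms.** Let R be the patients in the primary analysis set with residual tumour in either specimen, FN the Category B patients with residual tumour at surgery, and TN the Category B patients without it.

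- Endpoint definition: FN / R.
- Primary efficacy analysis as written: (TN + FN) / R.

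Category A patients have residual tumour by definition, and Category C patients are excluded from the set. So every patient in the set without residual tumour is Category B. With π the prevalence of residual tumour in the set, the written ratio is

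(1 − π)/π + FNR.

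**3. Put in numbers.** The protocol assumes a prevalence of at least 0.5. The values 0.6 and 0.7 are my assumptions, to show the range. There are 476 evaluable patients and the true FNR is 5%.

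| π | R | FN | TN | As written | Endpoint definition |
|---|---|---|---|---|---|
| 0.5 | 238 | 11.9 | 238 | 249.9/238 = 105% | 5% |
| 0.6 | 285.6 | 14.28 | 190.4 | 204.68/285.6 = 72% | 5% |
| 0.7 | 333.2 | 16.66 | 142.8 | 159.46/333.2 = 48% | 5% |

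At π = 0.5 and a true FNR of 10%, the written ratio is 110%.

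**4. Allow for where Category C falls.** These biopsies contain no tumour cells, so their exclusion may fall more on patients without residual tumour. Take the extreme in which it falls only on them, with 600 recruited and 300 having residual tumour. The 25% share is the plan's exclusion rate; 10% is my assumption.

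- Category C 10% (60 patients): (240 + 15)/300 = 85%.
- Category C 25% (150 patients): (150 + 15)/300 = 55%.

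**5. When could the written ratio reach 10% or less?** This needs π ≥ 1/(1.1 − FNR), which is 0.91 if the FNR is 0 and 0.95 if it is 5%. Both are far from the planning assumption.

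**6. When would the count exceed the number of trials?** At an FNR of 5% this needs π < 1/1.95 ≈ 0.513.

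**The case against.** The strongest reply is that nobody would run the literal formula. The sentence names its target as undetected residual tumour, and a true negative has none to miss. Two sections give the full numerator. The Sample size section equates the endpoint with false negative cases. Aims equates a rate below 10% with a sensitivity of at least 90%, which holds only for FN/R. The futility look also counts false negatives. On this view a clause was dropped, and the absurd result would be noticed at once. This stands as to what was intended. It does not make the sentence right, because it states an estimator outright and leaves nothing for a fuller plan to add.

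It could also be said that "estimated by the number of cases with diagnosed bpCR in VAB divided by the number of all patients for which surgery or VAB" uses cases as shorthand for patients with residual tumour. The sentence does not say so, and the two definition sections use the same word yet still spell out the surgical condition.

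A reader might infer more than the document supports:

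- **That the tested rate would be near 100%.** This holds only near a prevalence of 0.5, the lower bound of the planning assumption. The ratio falls to 48% at 0.7, and it depends on where Category C falls.
- **That the null hypothesis could never be rejected.** The accurate statement is that it could not be at any plausible prevalence.
- **That the count would exceed the number of trials.** At an FNR of 5% this needs an evaluable prevalence below about 0.513, a narrow edge of the stated range.
- **That the trial was designed around the wrong quantity.** Step 1 of the working shows that it was not.

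**Conclusion.** The point holds as an internal contradiction in the confirmatory section. The written estimator counts true negatives who are outside its denominator. At a true FNR of 5% it gives about 48% to 105% for prevalences from 0.7 down to 0.5, or 55% to 85% under the Category C extremes at a recruited prevalence of 0.5. The endpoint definition gives 5%. These figures rest on the assumed prevalences, FNR and Category C shares. The conclusion that the written ratio stays well above 10% does not depend on the exact choice within those ranges.

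The intended estimator can be recovered from the document. The hypotheses, α, denominator, analysis set and sample size of 238 cases are unaffected, so this is not a design flaw. It should still be corrected, because the sentence specifies the primary estimate and is wrong as it stands.

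**What to change.** In Primary efficacy analysis, replace the estimator sentence with one to this effect: p is estimated by the number of Category B patients who have residual tumour in the surgical specimen, divided by the number of patients in the primary analysis set who have residual tumour in the biopsy, the surgical specimen or both. This brings it into line with Outcomes and measurements and Derivation of the primary endpoint.

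The cost is one sentence. No new data, recalculation or change to the design is needed.

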#### Secondary analyses

All secondary endpoints are evaluated descriptively for the Primary Analysis Set (all recruited patients excluding “Category C”) as well as the Secondary Analysis Set (all recruited patients including “Category C”) in order to allow comparability and evaluation of the histopathological analysis. The secondary endpoints will be evaluated for the whole cohort and for six subgroups defined by.the tumor biology (TNBC, HER2+, and HR+/HER2-)the clinical / imaging response assessment (cCR, near cCR, cPR)the assessment of representativeness by specimen radiography.the subjective rating of the physician performing the biopsy.the different hospitals taking part in the study.the guidance method of the minimal invasive biopsy (ultrasound / stereotactic)

The investigators will provide point estimators and corresponding 95% confidence intervals for sensitivity, specificity, and diagnostic odds ratios for bpCR. Predictive values are obtained by using Bayes’ theorem based on the different prevalence estimates for bpCR in the full cohort, the subgroups mentioned above, and the trial centers.

The pathological evaluation of the VAB specimen (“pathological sub-study”, see above) will be assessed using Cohen’s Kappa where satisfactory agreement will be defined as an observed value of > / = 0.7.

Absolute and relative frequencies of adverse events are provided together with 95% confidence intervals.

We plan to perform an interim data look after having recruited and fully documented 300 participants. Within this interim look, no early testing for efficacy will be performed. However, it will be evaluated if a stop for futility seems indicated. A stop for futility could be indicated if the number of false negative cases is too large to reach the study aim (non-stochastic curtailment) or for other safety reasons.

## Discussion

To date, there are a number of closed, ongoing, and planned trials on this subject, described elsewhere in detail [27]:

As we do not know the maximum sampling error (= FNR) without impairing loco-regional control rates in case of omitting surgery, we deduced a maximum FNR of 10% from the results of the sentinel node trials. In these studies a false negative rate of 10% did not translate into a worse loco-regional or overall survival [28]. More recently, the ACOSOG Z0011 trial showed, that leaving lymph node metastases behind in about 20% of the cases, did not translate into worse loco-regional, disease-free and overall survival [29]. As the cohort of patients treated with NACT is a high risk population we decided for a reasonably low FNR.

During the study we anticipate a set of possible challenges in patient recruitment. First of all, the VAB intervention does not provide participating patients with a personal benefit. By contrast, it involves a second invasive intervention in addition to surgery. We thus assume patients to be reluctant to participate in the study. Hence, a proficient informed consent discussion with the patient and a detailed explanation of the study aim will be crucial for patient recruitment.

Another critical issue in VAB evaluation will be the histopathological evaluation of the representativeness of the VAB specimen. Differentiating accurately between a Category B (= pCR in VAB) and Category C (= possible sampling error) result will be decisive for the achievement of qualified study results. In the pilot study [25] anticipating this RESPONDER trial, the following stroma and cell reactions were used as criteria based on preceding reports [30–32]. Typical stroma reactions due to NACT included oedematous swelling or fibrosis. Within the fibrotic area a low cell-density was found. Stroma cell reactions were constituted of atypical adenoid cell complexes with large nuclei, regressively transformed residuals of atypical ductal epithelial proliferation, atypical ductal epithelial hyperplasia, or metaplasia of cylindrical cells. Furthermore, cell reactions included macrophage reactions such as the presence of foam cell-like macrophages, giant cells, hemosiderin-charged macrophages, or foam cells indicating resorptive processes. Round cell infiltrates and lympho-histiocytic inflammatory infiltrates were partly present. Based on these findings and experiences histopathological evaluation should allow a standardised diagnostic categorisation.

In case of study results which would permit rejection of the null hypothesis by yielding a false negative rate of less than 10%, VAB would be rated as an accurate diagnostic measure. Possible future trial scenarios would raise difficult questions: In this still hypothetical setting, studies on the therapeutical impact of surgery in bpCR cases would be the consistent consequence. However, the possible setting in which such a study could be realized remains unclear. Ethical and technical issues will have to be addressed for future trial designs. One future option might be a two-armed randomized controlled trial with radiotherapy only as local therapeutic management as one arm and surgery (with or without radiotherapy according to guidelines) as the other arm. Potential endpoints of such a trial might be disease free or in-breast recurrence free survival. Recruitment may be a challenge in a trial offering a non-surgical treatment arm. However, sooner or later the planning of possible future clinical trials on the omission of surgery in bpCR cases will have to be discussed.

## Abbreviations

bpCR: Pathological compete response in the breast
cCR: Clinical complete response
cPR: Clinical partial response
DFG: Deutsche Forschungsgemeinschaft (German Research Foundation)
EC: Ethics committee
FNR: False negative rate
ITT: Intention to treat
NACT: Neoadjuvant chemotherapy
NPV: Negative predictive value
pCR: Pathological compete response
PP: per-Protocol
PPV: Positive predictive value
VAB: Vacuum-assisted biopsy
